### Outcome measures

Data and samples will be collected at various time points, including baseline, mid-intervention (week 4), end of intervention (week 8), birthing and hospital discharge (medical records) and 6 weeks post-natally. All questionnaires will be self-administered and collected by the principal investigator. The primary outcome endpoint, reduction in depression severity, will be assessed at baseline, at 4 and 8 weeks from trial entry and at 6 weeks post-natally via the EPDS, an extensively validated, clinically sensitive [138], 10-item self-report questionnaire. Additional secondary outcome endpoints will also be examined as follows :At the same time points as the EPDS, reduction in stress and anxiety will be monitored with the 21-item Depression Anxiety and Stress Scale (DASS-21) [139] and improvement to quality of life will be evaluated using the 26-item World Health Organisation Quality of Life Scale (WHO-QoL-26,) [140]. The DASS-21 is a short form of the clinically validated [141] and cross-culturally reliable [142] self-report measure of emotional states of stress and anxiety. The WHO-QoL-26 [140] is also an abbreviated form of this discriminant, content valid, internally consistent and reliable self-report measure for overall quality of life.Adjustment to parenting and maternal-infant bonding will be evaluated at 6 weeks post-natally via the 13-item Being a Mother Scale (BaM-13) [143]. The BaM-13 is a clinically discriminating, reliable and valid self-report tool specifically designed to enable early assessment of women’s experiences of motherhood.Maternal-infant outcomes such as gestational diabetes, mode of delivery, method of pain relief, labour augmentation, post-partum haemorrhage, breastfeeding level and duration, gestational age at delivery, birth weight, 1- and 5-minute Apgar scores, neonatal intensive care unit admission and need and reason for resuscitation and or intensive care will be assessed at delivery, discharge and 6 weeks post-natally.Salivary OT levels will be determined using saliva specimens collected by the principal investigator at baseline and at 4 and 8 weeks from trial entry. Leucocyte OTR messenger RNA (mRNA) expression will be assessed using blood collected by phlebotomists at local pathology centres at baseline and 8 weeks from trial entry.

Every effort will be made to minimise missing data by ensuring weekly contact with participants during the intervention period as well as robust follow-up at later data collection points. Missing data for the primary endpoint of depression will be estimated using multiple imputation data derived from the K6 instrument. All missing data will be reported with reasons given and patterns of occurrence explored.

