### Randomisation and blinding

Participants and practitioners are not blinded to the study; however, data entry and analysis will be blinded. The randomisation schedule was computer-generated to contain three groups of random numbers, enabling stratification for the three different models of antenatal care (obstetrician, standard and caseload midwifery) as well as to randomly contain ‘blocks of three’ within each group, acupuncture, PMR or usual antenatal hospital care (1:1:1). The schedule was generated by the school statistician ([name]) and concealed in opaque envelopes by an independent researcher from the National Institute of Complementary Medicine (NICM) ([name]).

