The principal investigator of this trial ([name]) has 14 years of full-time clinical experience and will conduct all acupuncture sessions, unless unable, in which case a backup acupuncturist with 14 years of part-time clinical experience will be employed. Both practitioners have bachelor’s degrees in acupuncture and are registered with the Chinese Medicine Board of Australia and the Australian Acupuncture and Chinese Medicine Association. The principal investigator will also conduct all PMR sessions, unless unable, in which case a backup associate researcher will be employed.

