### Sample analysis

The principal investigator will process samples as follows. 4 ml of saliva will be obtained via passive drool into sterile CELLSTAR polypropylene test tubes (15 ml, catalogue number 188271; Greiner Bio-One, Frickenhausen, Germany), transported on ice and frozen and stored at −20 °C. Thawed samples will later be batch-processed and concentrated using equilibrated Sep-Pak C18 200-mg resin cartridges (catalogue number WAT 054945; Waters Corporation, Milford, MA, USA) before refreezing at −20 °C in 5-ml sterile Eppendorf tubes (catalogue number 0030119401, Eppendorf, Hauppauge, NY, USA). Triplicate OT concentrations will be batch-calculated using an OT enzyme-linked immunosorbent assay (ELISA) kit (catalogue number ADI-901-153A-0001; Enzo Life Sciences, Farmingdale, NY, USA) and an ELISA plate reader. Blood (2.5 ml) collected into PAXgene blood tubes (catalogue number 762165; BD Diagnostics, [name], USA) will be stored at −20 °C no sooner than 2 h after collection. Batch extraction of mRNA will later be performed using PAXgene blood RNA kits (catalogue number 762174; BD Diagnostics) and stored at −20 °C before cDNA libraries are made using iScript Advanced cDNA Synthesis kits (170-8843 Bio-Rad Laboratories, Hercules, CA, USA) and mRNA expression is determined by qRT-PCR using human OTR PCR primers (catalogue number VHPS-6555; Applied Biosystems, Foster City, CA, USA).

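### The unblinded principal investigator treats both active arms, collects the primary self-report form and is named as processing the samples, while blinding is stated only for data entry and analysis

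*Protocol article*

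**What the plan says.** Under Randomisation and blinding the article states: "Participants and practitioners are not blinded to the study; however, data entry and analysis will be blinded".

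Under Interventions, the principal investigator "will conduct all acupuncture sessions, unless unable, in which case a backup acupuncturist with 14 years of part-time clinical experience will be employed". The next arm is handled the same way: "The principal investigator will also conduct all PMR sessions, unless unable, in which case a backup associate researcher will be employed". Treatment is one hour a week for eight weeks in both active arms.

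Under Outcome measures, the primary endpoint is depression severity on the EPDS, described as a "10-item self-report questionnaire", at baseline, weeks 4 and 8, and 6 weeks post-natally. The collection rule covers every arm and every instrument: "All questionnaires will be self-administered and collected by the principal investigator". The principal investigator also collects the saliva. Phlebotomists draw the blood.

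Sample analysis opens with "The principal investigator will process samples as follows" and then lists extraction, the oxytocin ELISA and the receptor qRT-PCR in the passive voice. Treatment and assessment schedules says that collected data are de-identified. It does not mention coding of samples.

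The limitations in the Discussion include self-report, practice effects and the non-specific effects of procedures and interactions. They do not mention that therapist and collector are the same person.

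**The concern.** The stated blinding starts at data entry. By then the answers are already on the form. When the rater is an unblinded participant, the step that can still be protected is who receives the answer, and the plan gives that step to the therapist.

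The Abstract and Sample size both power the trial on acupuncture versus usual care. A woman in the acupuncture arm returns her EPDS to the person who has been treating her. A woman in usual care returns hers to someone with whom she has had much less contact. If treated women soften their answers out of courtesy, or report what they believe is hoped for, the error lowers EPDS scores in the acupuncture arm and looks like benefit.

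The mechanistic aim raises a second, weaker question. The person named as processing the samples knows the allocation, and the article does not say whether the promised blinding of analysis reaches the laboratory. The Background itself faults earlier trials for unclear assessor blinding.

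**Working it through.** **Roles side by side.**

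- Knows the allocation: the practitioner (Randomisation and blinding).
- Gives acupuncture and PMR: the principal investigator, with backups (Interventions).
- Receives all questionnaires and collects saliva: the principal investigator (Outcome measures).
- Processes samples: the principal investigator, named once (Sample analysis).
- Blinded: data entry and analysis only. No collector independent of treatment is named.

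**Contact by arm.** Both active arms have up to eight one-hour sessions with the same therapist, so acupuncture versus PMR is largely balanced on this route. Usual care has a case history and diagnosis at entry (Interventions), a weekly Kessler 6 (K6) by telephone (Safety monitoring) and the same collector of forms and saliva. Contact in usual care is real but much smaller, so the powered contrast is not balanced.

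**Illustration of scale.** The point rests on no figure in the plan, and the documents give no size for the bias, so the shifts below are assumptions.

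Inputs from Sample size: SDs 5 and 6.5, target difference 13 − 8.9 = 4.1 points, two-sided 5 %. Arm sizes are 75/3 = 25 and 96/3 = 32. The plan's 75 is used only to give an arm size. With these inputs a two-sided test at 80 % power needs 32 evaluable women per arm, not 25, which is a separate matter.

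Standard error of the difference = √[(5² + 6.5²)/n] = √(67.25/n):

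- n = 25: √2.690 = 1.64
- n = 32: √2.102 = 1.45

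With no true effect and an additive bias b, type I error = 1 − Φ(1.96 − b/SE) + Φ(−1.96 − b/SE).

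Example for b = 1 and n = 25: b/SE = 0.61, so 1 − Φ(1.35) + Φ(−2.57) = 0.089 + 0.005 = 0.094.

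| Assumed bias (EPDS points) | Share of 4.1 | n = 25 per arm | n = 32 per arm |
|---|---|---|---|
| 0.5 | 12 % | 6.1 % | 6.4 % |
| 1 | 24 % | 9.4 % | 10.6 % |
| 1.5 | 37 % | 15.0 % | 17.9 % |
| 2 | 49 % | 23.0 % | 28.1 % |

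**The imputation route.** K6 is taken in the session for the active arms and by telephone for usual care (Safety monitoring). It also supplies the multiple imputation of missing primary data (Outcome measures). A difference in collection between arms can therefore reach imputed EPDS values as well.

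**The case against.** The strongest reply is that the women are unblinded and rate themselves, so their own expectation stays in the score whoever takes the form. That stands. Independent return removes only the part directed at the therapist.

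The design also answers some of this. Overview assigns the estimation of non-specific effects to the PMR arm, which has the same therapist, dose and collector, and the Discussion acknowledges non-specific effects of interactions. That stands for acupuncture versus PMR, but that is not the contrast for which the trial is powered.

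Three stronger readings are tempting, and the article does not support them:

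- A reader might infer that women hand over the EPDS straight after being treated. The article does not say when in relation to the session, whether in person, or whether open or sealed. At 6 weeks post-natally no session has just taken place.
- A reader might infer that usual-care women have no relationship with the study team. They have an entry case history, weekly telephone contact and the same collector, and are offered four acupuncture sessions after final data collection.
- A reader might infer that the assays are run unblinded. That rests on one opening sentence, with the assay steps in the passive voice. The statement "data entry and analysis will be blinded" may have been meant to include the laboratory. Triplicate oxytocin measurement, batch processing and a plate reader also limit discretion.

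**Conclusion.** The point holds as a narrow design weakness. The article states, rather than merely leaves out, that one unblinded person gives nearly all treatment in both active arms and collects the primary self-report outcome. In the powered contrast this leaves open an avoidable route for response bias that can favour acupuncture. For the assays the conclusion is conditional: either the samples are not masked from the person who processes them, or two sections need reconciling.

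The size is unknown. The figures of about 9–11 % for 1 point and 23–28 % for 2 points assume an additive bias in one direction, no true effect, the planning SDs, a normal approximation and 25 to 32 women per arm. They describe total bias of that size. They should not be read as what a change of collector would recover, because part of any such bias is the woman's own expectation. Nothing here invalidates the trial. It is a cheap improvement that should be made.

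**What to change.** - **Outcome measures:** have women return the EPDS, DASS-21, WHO-QoL-26 and BaM-13 in sealed, pre-coded envelopes, by post or online, to the blinded data-entry role, unopened by the practitioner. Use the same mode in all arms. Keep the week-8 form at the end of intervention, after the eighth session. Moving it ahead of that session would measure before treatment is complete.
- **Randomisation and blinding, and Sample analysis:** state that tubes carry codes hiding arm and time point from whoever runs the ELISA and qRT-PCR until results are locked. If the blinding of analysis already covers the laboratory, say so and reconcile the two sections.
- **Discussion:** add the overlap of therapist and collector to the limitations. Acknowledge that K6 is collected differently by arm and feeds the imputation of the primary endpoint. The changes above do not close that route.

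Trial status gives recruitment as ongoing, so remaining forms can be rerouted and samples not yet assayed can be recoded. Make the change in all arms on one recorded date.

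The cost is envelopes or an online form, slightly slower return and a small recoding task for someone not involved in treatment. The weekly K6 safety check is unchanged.

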### Safety monitoring

Owing to the morbidity of this population, women will undergo a weekly psychological assessment with the Kessler 6 (K6) instrument [110], either during the weekly session (intervention groups) or by telephone (usual care). If notable worsening or a ‘cut-off’ score is reached, immediate referral will be made to hospital antenatal mental health services. Any adverse events arising from the acupuncture intervention will be documented and reported to Western Sydney University and the South West Sydney Local Health District, and prevalence will be calculated. Such events are reportedly rare (occurring approximately 1.3 times every 1000 treatments) and generally of a mild [111, 112] to moderate nature [112]. However, if such events do occur, participants will be reminded of their right to withdraw from the study at any time.

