### Sample size

Mean antenatal EPDS scores extracted from a recent Australian study [111], as well as estimated post-intervention between-groups differences derived from a meta-analysis of two antenatal depression acupuncture studies [9], were used for a power calculation for this study. Using a power of 80 % and two-sided testing at a 5 % significance level, detecting a significant difference in end of intervention mean ± standard deviation (SD) EPDS scores of 8.9 ± 5 for the acupuncture group plus usual hospital care versus 13 ± 6.5 for usual hospital care will require a total recruitment goal of 75 participants. As high attrition rates have been reported for this population [144], an additional recruitment of 30 % has been added, resulting in a total goal of 96, or 32 participants per group.

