### Statistical analysis

Descriptive statistics will be used to describe the characteristics of the study population. An intention-to-treat analysis will be undertaken [145], with between-groups differences explored using analysis of variance for the primary and secondary endpoints of depression, stress, anxiety, quality of life and OT/OTR. Effect sizes will be reported with 95 % confidence intervals, and results will be considered significant if *p* values are less than 0.05.

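### Imputation is stated for the primary EPDS endpoint only, so the ANOVA of stress, anxiety, quality of life and OT/OTR is, as written, an available-case analysis under an intention-to-treat label

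*Protocol article*

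**What the plan says.** Three parts of the Protocol article bear on this.

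- **Outcome measures, missing-data paragraph.** A method for filling in missing values is given for one endpoint: "Missing data for the primary endpoint of depression will be estimated using multiple imputation data derived from the K6 instrument". For everything else the commitment is descriptive: "All missing data will be reported with reasons given and patterns of occurrence explored". Prevention is also promised: "Every effort will be made to minimise missing data by ensuring weekly contact with participants during the intervention period".
- **Statistical analysis.** The label is "An intention-to-treat analysis will be undertaken", and the same sentence fixes the estimator and its scope: "between-groups differences explored using analysis of variance for the primary and secondary endpoints of depression, stress, anxiety, quality of life and OT/OTR".
- **Sample size.** Loss is expected: "As high attrition rates have been reported for this population [144], an additional recruitment of 30 % has been added". The goal goes from 75 to 96, or 32 per group.

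Outcome measures also sets the schedule. The DASS-21 and WHO-QoL-26 are taken at baseline, weeks 4 and 8, and 6 weeks post-natally. Salivary oxytocin is taken at baseline and weeks 4 and 8. Leucocyte OTR is measured at baseline and week 8 only.

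**The concern.** The intention-to-treat label and the ANOVA cover primary and secondary endpoints alike, but the stated imputation covers only the primary one. Ordinary ANOVA has no means of including a woman whose outcome is missing. If the two sections are followed as they stand, the DASS-21, WHO-QoL-26 and OT/OTR comparisons use whoever supplied a value at that visit. If the ANOVA is a classical repeated-measures one, any missed visit removes the woman altogether.

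Loss that differs between arms is plausible here. Participants are not blinded. Usual care gets a weekly telephone K6 rather than sessions, and is offered acupuncture only after the final data are in. If women doing badly leave one arm more readily than another, those who remain are no longer comparable. For women lost after week 4, a week-8 ANOVA also ignores their week-4 scores, which say something about how they were doing. The Background hypotheses on stress, anxiety, quality of life and the oxytocin system rest on these analyses.

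**Working it through.** **1. How much loss the plan allows for.** Inputs, from Sample size: 75 before the allowance, 30 % added, 96 in total, three equal groups.

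- 75 × 1.30 = 97.5. Per group, 25 × 1.30 = 32.5, taken as 32, and 3 × 32 = 96. The goal is reproduced up to rounding.
- Loss covered: 1 − 75/96 = 21.9 %, which is 96 − 75 = 21 women, or 7 per arm.
- A 30 % loss is a different quantity. It would leave 96 × 0.70 = 67 women, and keeping 75 would need 75/0.70 = 107.1, or 108 in three equal groups.

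The 75 itself is taken here as the plan gives it. It does not follow from the stated two-sided inputs: the SD is √((5² + 6.5²)/2) = 5.80, and 2 × (1.96 + 0.84)² × 5.80²/4.1² gives 32 per group, or 96 evaluable women. That is a separate matter and does not alter this point.

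**2. What the two sections imply together.**

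| Endpoint | Analysis stated | Handling of missing values stated |
|---|---|---|
| EPDS | ITT, ANOVA | Multiple imputation from K6 |
| DASS-21 stress, anxiety | ITT, ANOVA | Reasons reported, patterns explored |
| WHO-QoL-26 | ITT, ANOVA | Same |
| Salivary OT, leucocyte OTR | ITT, ANOVA | Same |

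**3. Possible size of the bias.** The article gives no effect size, SD, visit correlation or drop-out mechanism for these endpoints, so every input to this simulation is an assumption:

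- acupuncture versus usual care, scores in SD units, with higher scores worse;
- true difference 0.30 SD at week 4 and 0.50 SD at week 8;
- correlation between visits 0.5 to 0.7;
- 22 % loss in each arm, all of it after week 4;
- log-odds of loss = a + b × week-4 score, with a set to give 22 % and b chosen by arm (size 1 per SD where loss depends on score).

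The available-case estimate is the difference between the observed week-8 means.

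| Loss pattern | Available-case estimate (true 0.50) | Shortfall |
|---|---|---|
| Random, or same pattern in both arms | 0.50 | none |
| Worse scorers leave usual care; unrelated to score under acupuncture | 0.41 to 0.37 | 0.09/0.50 to 0.13/0.50 = 18 to 26 % |
| Worse scorers leave usual care, improved women leave acupuncture | 0.31 to 0.23 | 0.19/0.50 to 0.27/0.50 = 38 to 54 % |

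With the slope halved to 0.5, the usual-care-only pattern gives 0.45 to 0.43, a shortfall of 10 to 14 %. An estimate that also uses each woman's baseline and week-4 values within arm returned 0.49 to 0.51 in these runs. If the patterns were reversed between arms, the bias would reverse too.

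**4. Limit of step 3.** Loss was generated from the observed week-4 score, which is the condition under which using that score recovers the truth. In a separate run, loss depended on the unseen outcome itself, in opposite directions by arm (slope 0.7, correlation 0.5, realised loss 24 % and 30 %). The available-case estimate fell to 0.15. A method that assumes missing at random would not fully repair that case.

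**The case against.** The strongest objection is that this builds on silence. The article does not say that secondary endpoints will not be imputed. Handling of missing secondary outcomes is often left to an analysis plan or full protocol, neither of which is shown, so its absence alone is no finding. The sections also do not say whether the ANOVA is by visit or repeated-measures. Some would hold that intention-to-treat is satisfied by analysing women in their assigned arm. The endpoints are secondary, and the promised look at missing-data patterns could reveal loss that differs by arm.

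Much of this stands, and it rules out stronger readings that a reader might infer:

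- **That the plan prescribes a completers-only analysis.** No sentence says so. Available-case follows from ordinary ANOVA with nothing added.
- **That 30 % attrition is planned.** The 30 % is extra recruitment. The loss it covers is about 22 %.
- **That women who leave are scored for EPDS but dropped elsewhere.** The plan says "women will undergo a weekly psychological assessment with the Kessler 6 (K6) instrument", at sessions or by telephone. A woman who has left may supply no later K6, and none is stated at 6 weeks post-natally. How well her EPDS can be imputed is unknown.
- **That the secondary results will be biased.** Step 3 shows no bias under random loss or the same pattern in both arms. An unblinded design makes loss that differs by arm possible, not established.

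What survives does not depend on silence. The article publishes a missing-data rule, states it for one endpoint, and names an estimator and an intention-to-treat label for the others. That estimator cannot include women without a value, and a better one is available from data already scheduled.

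**Conclusion.** The point holds in a limited form. As described, the ANOVA of DASS-21 stress and anxiety, WHO-QoL-26 and OT/OTR is an available-case analysis carrying an intention-to-treat label. It is open to bias only if loss depends on a woman's condition differently by arm. At the roughly 22 % loss that the goal of 96 covers, a true 0.50 SD could be estimated anywhere from about 0.23 SD to without bias across the score-dependent patterns in step 3. Those figures rest on assumed effects, correlations, timing of loss and strength of dependence. They show what is possible and do not forecast what will happen. The primary endpoint is not affected by this point, so it is a change that should be made rather than a threat to the trial's main conclusion.

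**What to change.** In Outcome measures (missing data) and Statistical analysis, do one of the following for DASS-21 stress and anxiety, WHO-QoL-26 and salivary oxytocin:

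- replace ANOVA with a linear mixed model for repeated measures that uses all collected visits, with arm, visit and arm-by-visit terms, and read the between-arm difference at each visit from it; or
- extend multiple imputation to these endpoints, within arm, using their own baseline and week-4 values.

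OTR has a single follow-up measurement, so label its analysis available-case.

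The cost is wording and slightly more analysis work, with no new visits, samples or participants. Both options rely on missing at random, so loss that depends on unseen values would not be fully corrected, and the text should say so.

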### Treatment and assessment schedules

The study period will run for 8 consecutive weeks from gestation week 24 to the end of week 31 (Fig. 1). At baseline, age, gestational age, number of previous pregnancies and/or births, relationship status and/or quality, education, employment status and country of birth will be collected, along with depression-related clinical data, including medical diagnoses, entry EPDS score, age of onset and length of index episode, number and severity of past depressive episodes, length and severity of current episode, family history of depression and current medication and/or psychotherapy use. Collected data will be de-identified and securely stored at the NICM.

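### The K6 is the only source named for imputing missing EPDS, yet the visible schedule gives no concurrent K6 for the post-natal EPDS and ties K6 to session attendance in the treated arms

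*Protocol article*

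**What the plan says.** The missing-data paragraph at the end of Outcome measures reads: "Missing data for the primary endpoint of depression will be estimated using multiple imputation data derived from the K6 instrument". It names no other variable. The same paragraph undertakes to limit missing data by "ensuring weekly contact with participants during the intervention period as well as robust follow-up at later data collection points", and to report reasons and explore patterns.

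The K6 itself is described under Safety monitoring: "women will undergo a weekly psychological assessment with the Kessler 6 (K6) instrument", taken "either during the weekly session (intervention groups) or by telephone (usual care". Treatment and assessment schedules gives the period: "The study period will run for 8 consecutive weeks from gestation week 24 to the end of week 31".

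Outcome measures says that the primary outcome, depression severity, "will be assessed at baseline, at 4 and 8 weeks from trial entry and at 6 weeks post-natally via the EPDS". The DASS-21 and WHO-QoL-26 are taken at the same points, and the Being a Mother Scale is added post-natally. No K6 is mentioned at that visit. Under Interventions, a telephone or recorded session for a woman who cannot attend is stated for the relaxation arm only.

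**The concern.** Imputation can only draw on what was collected, and the named source does not match the outcome schedule in three respects.

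- **Timing.** The post-natal EPDS is one of three follow-up points of the primary outcome, but the visible text gives no K6 near it.
- **Attendance.** In the treated arms the stated route for K6 is the session. A woman who leaves acupuncture may therefore lose the predictor along with the outcome. The usual-care route does not depend on attendance. Acupuncture against usual care is the contrast that was powered.
- **Model content.** If the sentence is followed as written, neither treatment arm nor earlier EPDS enters the model. Imputed values are then drawn towards a relation common to all arms, and the estimated difference moves towards zero.

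Missing data are not a side issue here. The Sample size section opens its allowance with: "As high attrition rates have been reported for this population".

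**Working it through.** **1. Schedules side by side (protocol article).**

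| EPDS time point | K6 in the visible text |
|---|---|
| Baseline, week 4, week 8 | Weekly over gestation weeks 24 to 31, all arms |
| 6 weeks post-natally | None described |

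Age of the last K6 at the post-natal visit, assuming birth at 40 weeks: 40 + 6 − 31 = 15 weeks.

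**2. How many values could be imputed.** Taking the Sample size totals as printed, 96 − 75 = 21 women may be lost. That is 21/96 = 21.9 %, or 32 − 25 = 7 per arm.

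**3. Effect of imputing from K6 without arm (illustration).**

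*From the Sample size section:* week-8 means 8.9 and 13, SDs 5 and 6.5. The difference is 4.1 and the mean within-arm variance W = (25 + 42.25)/2 = 33.625.

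*Assumed, not in the documents:* values missing completely at random in fraction p; K6 = 0.5 × EPDS + noise, with K6-EPDS correlation r of 0.6 or 0.8; two arms; large samples. Noise variance is V = (0.5 × 5.8)² × (1/r² − 1), where 5.8 is √W rounded.

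The pooled slope of EPDS on K6 is b = [0.5W + 4.1D/4] / [0.25W + V + (D/2)²], where D is the arm difference in mean K6. The estimated difference is (1 − p) × 4.1 + p × b × D.

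With no difference between telephone and session readings, D = 0.5 × 4.1 = 2.05:

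- r = 0.6: V = 14.95, b = 18.91/24.41 = 0.775, bD = 1.59.
- r = 0.8: V = 4.73, b = 18.91/14.19 = 1.333, bD = 2.73.

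At p = 21/96:

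- r = 0.6: 0.781 × 4.1 + 0.219 × 1.59 = 3.55.
- r = 0.8: 0.781 × 4.1 + 0.219 × 2.73 = 3.80.

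A simulation under the same assumptions with 20 % and 30 % missing gave 3.3 to 3.8, which agrees.

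**4. If telephone K6 reads differently from session K6 (simulation, 20 % and 30 % missing).**

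| Assumed shift in usual-care K6 | Difference, arm omitted | Difference, arm included |
|---|---|---|
| −2 to −1 | 2.9 to 3.6 | about 4.1 |
| 0 | 3.3 to 3.8 | about 4.1 |
| +1 | 3.6 to 4.0 | about 4.1 |

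The shrinkage is not guaranteed for every shift. With +2 and r = 0.8, D = 4.05, b = 20.96/17.24 = 1.216 and bD = 4.93, so at p = 21/96 the result is 3.20 + 1.08 = 4.28, above 4.1. With arm in the model, a constant shift is absorbed whatever its sign.

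**5. What this does not cover.** Steps 3 and 4 assume that a K6 exists for every missing EPDS and that dropout is unrelated to mood. They say nothing about women for whom both scores are absent, nor about the post-natal visit.

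**The case against.** The strongest reply is that one sentence in a journal article is not an imputation model. It names a source without excluding others. Arm, baseline EPDS and further predictors are ordinarily set in an analysis plan, which is not shown here. Much of this stands, and it limits the point in five ways.

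- A reader might infer that K6 is to be used alone. The text does not say so; it is the only source named, no more. The shrinkage in the working applies only if the sentence is followed literally.
- A reader might state as fact that K6 stops at week 8. That is an inference from the 8-week schedule and from "weekly contact with participants during the intervention period". The Fig. 1 legend includes K6, but the figure was not available for this review.
- A reader might conclude that the telephone/session difference by itself makes the imputation asymmetric. It does not: a constant shift vanishes once arm is modelled.
- The weekly assessment is promised to all women, and weekly contact is not limited by arm or attendance. It may reach non-attenders, and a usual-care woman may equally stop answering the telephone. Joint loss of K6 and EPDS is therefore possible but not established.
- At week 8, the point used for the power calculation, K6 is scheduled in every arm.

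Deferral to an analysis plan does not dispose of the rest. The article positively names a source, and its own visible schedule does not supply that source at one primary time point. No later plan can recover K6 scores that were never taken.

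**Conclusion.** The point holds in limited form. The one named imputation source has no concurrent value in the visible text for the post-natal EPDS, the last K6 being about 15 weeks earlier if birth is at term. It may also be missing together with the EPDS when an acupuncture participant stops attending.

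On the printed totals, about 22 % of values, 7 per arm, could be affected. If K6 were used without arm and read alike in both settings, a true 4.1 would be estimated at about 3.55 to 3.80, a loss of 0.3 to 0.55 points. This rests on the assumed correlations and on values missing completely at random.

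Two stronger readings should not be drawn. The 30 % in the Sample size section is an addition to recruitment, not a 30 % loss, so it does not imply about 10 imputed values per arm. Nor do the documents support a bias of particular size favouring acupuncture: nothing in them says how women who drop out would score, and the direction of bias from selective dropout is unknown.

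**What to change.** **Imputation.** Replace the sentence with one that imputes EPDS within arm, or with arm in the model, from baseline and all observed EPDS, DASS-21, model of care and weekly K6. With about 25 observed women per arm, a single model with arm as a term will be more stable than separate models with many predictors.

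**Post-natal EPDS.** Say that it does not rest on K6. The week-8 EPDS is about as old as the last K6, but it is the same scale and needs no conversion.

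**Collection.** State that the weekly K6 is taken by telephone in every arm when a session is missed. If this is already what is meant, the sentence only makes it explicit. If Fig. 1 shows a post-natal K6, add it to the text.

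**Cost.** Slightly more analysis work and a few short calls by a route already used for usual care. Recruitment was ongoing when the article was published, so the collection change could still have been made. A mixed model as the primary analysis, or a sensitivity analysis that worsens imputed acupuncture values, would be reasonable additions, but they are matters of preference and this point does not depend on them.
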